### Electrophysiological criteria

The median and ulnar nerve conduction velocity (NCV) study is performed according to the guidelines of the American Association of Neuromuscular & Electrodiagnostic Medicine for CTS [52]. Surface recording electrodes are placed over the motor point of the abductor pollicis brevis muscle for the median nerve and over that of the abductor digiti minimi for the ulnar nerve. The reference electrode is placed over the tendon. Maximum motor conduction velocity was calculated from elbow to wrist for the median nerve and below-elbow to wrist for the ulnar nerve. Distal motor latency (DML) is measured with a distance of 7 cm between the stimulation point of the nerves at the wrist and the above mentioned muscles. DMLs are measured from the stimulus onset to the initial negative response, and amplitudes are measured from baseline to negative peak. Electrical stimuli are delivered by a constant current stimulator through bipolar surface electrodes. The sensory nerve action potentials are recorded orthodromically with stimulating ring electrodes placed around the proximal and distal interphalangeal joints. Maximum sensory conduction velocity and maximum sensory action potential amplitude (SAPa) of the median (M3, middle finger-wrist; M4 ring fringer-wrist) and ulnar (U4 ring finger-wrist) nerves are determined. The difference between U4-M4 SCV is also calculated. Skin temperature was maintained > 32°C with an infrared lamp and recorded with a digital thermometer. Neurographic values at least 2 SD above or below the mean of the normative data of our laboratory (see below) are considered abnormal. Patients are eligible for the study if electrodiagnostic studies demonstrates any one of the following: I) abnormal comparative test i.e. a difference of >10 m/s between sensory conduction velocity of the median (M4) and ulnar (U4) nerves; II) abnormal digit/wrist sensory conduction velocity (M3 < 45 m/s and/or M4 < 43 m/s) and normal distal motor latency (DML <4.3 ms) of the median nerve. In other words, we will select only patients belonging to class I and II of the electrophysiological classification of CTS severity reported by Padua et al. [53], excluding subjects with absence of the sensory action potential or delayed DML or absence of the compound muscle action potential (CMAP) of the median nerve.

Finally, recruitment properties of the median nerve were studied by analyzing the relationship between the intensity of electrical stimulation and the size of motor and sensory responses, i.e. the input-output curve (I-O curve). This technique is capable to reveal focal conduction slowing in the median nerve, not detectable by conventional electrodiagnostic tests, in mild CTS patients [54,55]. In fact, the relationship between the stimulus intensity (input) and the size of the response (output) defines the characteristic of motor/sensory axon recruitment and, in addition to conventional parameters such as maximum amplitude, latency and maximum conduction velocity of a peripheral nerve, allows us to analyse the following variables: a) threshold value (the initial component), reflecting the most excitable axons; b) slope (the second component), indicating the recruitment efficiency (gain); c) plateau phase (the third component), reflecting the maximal size of CMAP, as well as the activation of axons that are ultimately recruited.

In order to determine the relationship between the intensity of electrical stimulation and the size of the median nerve motor response, the stimulating electrode is initially placed over the wrist, and its position adjusted until the site with the lowest threshold for eliciting a CMAP of 0.1 mV (baseline-negative peak) will be established. In order to determine median nerve (M3) SAPa we use the threshold that produced a SAPa of 1 uV; all sensory responses will be averaged. Stimulus intensities are increased in steps of 0.2 mA until the maximum (motor and sensory)-wave will be obtained. I-O relationship data will be fitted to a Boltzmann sigmoidal function by the Lavenberg-Marquard non linear least-mean-square algorithm [56]. Recruitment curves are constructed by normalizing stimulus currents and response amplitudes. This enabled comparison of individual I-O relationships. Parameters of the curves obtained before treatment will be compared with those obtained one, six and 1 year months later.

The same neurophysiologist will perform all electrodiagnostic tests at baseline and follow-ups.

### Ultrasonographic criteria

High-resolution ultrasonographic examination at wrist is a powerful tool in the diagnosis of compression mononeuropathies, particularly CTS [57,58] and allows to eliminate rheumatological pathology: arthritis, deforming arthrosis, flexor tenosynovitis, trigger finger.

In the uncertain situations standard rx is performed.

High-resolution ultrasonographic examination is performed by the same rheumatologist, experienced in musculoskeletal disorders, after electrodiagnostic test. A real-time scanner (Esaote Technos Mp) with a 5-10 MHz linear array transducer will used. Patients are seated in a chair with arms extended, hands resting in a horizontal supine position on the examination couch, and fingers semi-extended. It will perform longitudinal and transverse scans of the median nerve from the distal segment of the forearm to the tunnel outlet. The median nerve cross-section area (CSA) is measured at the tunnel inlet (just before the proximal margin of the flexor retinaculum) because the highest concordance with nerve conduction study is detected. CSA measurements are performed at the inner border of the thin surements hyperechoic rim of the nerve (perineurium) using the manual tracing technique. The weight of the probe is applied without additional pressure. The intra-observer reliability for nerve measurement has been tested previously and published elsewhere [59]. The same expert will perform all ultrasonographic examinations at baseline and during the follow-ups.

### Treatment

Patients are randomly allocated to one of two groups: (i) single cortisone (Triamcinolone acetonide 20 mg/1 ml, Triamvirgi, Fisiopharma), or (ii) single progesterone (Hydroxyprogesterone caproate 170 mg/1 ml, Lentogest, A.M.S.A.) echo-guided injection. If bilateral symptoms are present, only the hand the patient retains as having the most severe symptoms will be treated. The randomization is done with a dedicated script in MS Office Excel^®^. Since the injected substance can be easily identified by the treating rheumatologist, the only persons blinded to the treatment, beside the patient, will be the professionals performing the echography and the electrophysiology tests.

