### Study population

Patients were enrolled in the study if the symptoms compatible with clinical diagnosis of CTS were confirmed by electrodiagnostic evidence of delay of the distal conduction velocity of the median nerve (for details see respective paragraphs).

Patients who are eligible for participation will be informed about the trial by the neurologist. If they show interest, they will receive written information about the trial with a detailed description of the aim of the study and of the implications of participation. Only subjects able to read, understand and sign the informed consent are included in the study. The information about the trial is also missed to the general practitioner of the patient.

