### Clinical criteria

Patients with suspected CTS referred to our electrodiagnostic laboratory to confirm clinical suspicion of CTS will be eligible for including in the trial from 01.06.2008. Patients will be recruited if they will complain at least three months of the following symptoms: nocturnal awaking or activity-related numbness, tingling, burning, pain in the hand distribution of the median nerve according to hand diagram by Katz et al. modified by consensus criteria of classification of the CTS. Only "classic/probable" and "possible" cases will be enrolled [47,48]. Then only patients with "mild" CTS will be successively included in the trial. Mild cases are defined as those patients who complain only symptoms without objective sensory loss, weakness of abduction/opposition of the thumb and hypotrophy/atrophy of thenar eminence, i.e. these patients belonging to stage 1 and 2 of a validated clinical CTS severity scale [49]. Other mandatory inclusion criteria are female gender (because the progesterone is a natural female hormone) and age between 18 and 60 years.

Exclusion criteria are: previous conservative or surgical treatments for CTS, diabetes, connective tissue and thyroid diseases, renal failure, gout, pregnancy, lactation, estrogen drugs, arthritis and deforming arthrosis, onset of CTS symptoms after hand trauma, polyneuropathy, brachial plexopathy, neuropathy of the ulnar nerve at elbow, thoracic outlet syndrome and history of cervical radiculopathy.

Physical examination consisted of evaluating of muscular strength and trophism, sensory function, evocation of deep reflexes and provocative clinical test (Phalen and Tinel signs) will be performed by neurophysiologist before the electrodiagnostic tests.

For subjective evaluation of severity of symptoms, the Boston Questionnaire will be completed by patients just before the injection [50,51]. The questionnaire is divided into two parts. The first part (11 items) evaluates symptoms, and the second part (8 items) evaluates the functional status of the hand. Five answers are possible to each question; they are scored 1 to 5 according to the severity of symptoms or the difficulty of performing a certain activity. Each score is calculated as the mean of the score of individual item. Severe impairment is indicated by a high score.

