### Sample size

The main output parameter is the Symptom Severity Scale (SSS) score of the self-administered Boston Carpal Tunnel Questionnaire. The values reported in the literature assessing the cortisone treatment effect after 2 and 3 months are ranging between 1.37 - 2.3 (mean ± standard deviation: 1.6 ± 0.7). It has been estimated that a minimum number of n = 26.2 subjects for each group would be necessary to reveal a significant (α = 0.05) decrease in the SSS score from 1.6 to 2.0 with enough power (90%). If a drop-out of 4 subjects is considered, the minimum number of subjects required should be adjusted to no. = 30.

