### Data analysis

The values for each recorded parameter (NCV, CSA, BQ, VAS) will be submitted to a two-way ANOVA, with the main factors TREATMENT (cortisol vs progesterone) and TIME (baseline, 1 month, 6 months, and 12 months after the injection). The significance level will be set at *p *< 0.05. Tukey's test post-hoc analysis will be performed when necessary, in order compensate for possible type I errors.

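### The closed list of blinded persons is wider than its reason: only the injector cannot be blinded, yet questionnaire and VAS handlers and the analyst are left off the list too (minor)

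*Protocol article*

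**What the plan says.** The Treatment section of the protocol article opens its statement on blinding with a reason, "Since the injected substance can be easily identified by the treating rheumatologist", and draws from it that "the only persons blinded to the treatment, beside the patient, will be the professionals performing the echography and the electrophysiology tests".

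Other sections show who does what:

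- Sample size: "The main output parameter is the Symptom Severity Scale (SSS) score of the self-administered Boston Carpal Tunnel Questionnaire". The Design of the trial section puts the pain VAS beside it as part of the major outcome, with visits at baseline and at 1, 6 and 12 months.
- Clinical criteria: at baseline, "the Boston Questionnaire will be completed by patients just before the injection". The same section says that the VAS is administered and that the patient is told how to mark it. It does not say by whom.
- Electrophysiological criteria: "The same neurophysiologist will perform all electrodiagnostic tests at baseline and follow-ups".
- Ultrasonographic criteria: "The same expert will perform all ultrasonographic examinations at baseline and during the follow-ups".
- Data analysis: a two-way ANOVA of treatment by time for each recorded parameter, after which "Tukey's test post-hoc analysis will be performed when necessary". No analyst is named.

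**The concern.** The reason and the rule do not match in scope. That the injector can recognise the drug explains why that one person cannot be blinded. It does not explain why the person who hands out forms, the person who explains the VAS or the person who runs the analysis should know the arm. The wording is exclusive, so these roles are not simply left undescribed: the sentence places them outside the blind.

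Two protections are at stake. First, the major outcome is patient-reported. It is protected as long as the patient stays unaware of the arm and is not prompted, and someone who knows the arm and talks to her at follow-up could weaken that. Second, the stated aims are directional in favour of progesterone. An analyst who sees arm labels while deciding whether a post-hoc test is needed can, without intending to, lean towards the hoped-for result.

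**Working it through.** No arithmetic settles this point. It rests on setting the stated list against the roles that the article describes.

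1. **Patient.** Rates the symptom score and the VAS. On the blinded list.
2. **Electrophysiology tester.** One neurophysiologist for all visits. On the list.
3. **Ultrasound examiner.** One rheumatologist for all visits. On the list.
4. **Injecting rheumatologist.** Not on the list, and the stated reason applies.
5. **Whoever explains the VAS and handles the Boston Questionnaire at 1, 6 and 12 months.** Not named and, in that role, not on the list. The stated reason does not apply. If one of the two blinded testers does this, the person is blinded, but the article does not say so.
6. **Whoever runs the ANOVA and decides on the Tukey tests.** Not named and not on the list. The stated reason does not apply.
7. **Whoever runs the Excel randomisation script.** Not on the list. This person must hold the allocation, so cannot be blinded, but for a different reason from the one given.

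Roles 5 and 6 are therefore outside the blind with no reason given.

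How could this reach an outcome?

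- **Nerve conduction and ultrasound area.** Both are measured by blinded testers, so no measurement route is open.
- **Symptom score and VAS.** The rater is the blinded patient. The only route is through role 5, by prompting or by the way the VAS is explained, or through a remark that reveals the arm.
- **Analysis.** The model, its factors, the time points, the significance level and the post-hoc test are all named. What stays open is when the post-hoc test is run, and role 6 decides that.

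Both open routes are indirect. The document gives no figure from which a size could be worked out.

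**The case against.** The strongest case on the other side is that every outcome rater is already blinded, that the article never describes an analyst, and that coded arms and data lock are commonly left to a fuller document. On this view the sentence merely explains why the injector cannot be masked, and its exclusive wording should not be pressed.

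The first part stands and is why the point is minor. The rest does not dispose of it. The article does not stay silent on who is blinded. It states a closed list, and a fuller plan that blinded the analyst or the questionnaire handler would contradict that list.

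Several stronger readings are tempting, and the document does not support them:

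- **That the neurologist who recruits is left unblinded.** The Study population section says only that "Patients who are eligible for participation will be informed about the trial by the neurologist". This comes before allocation, where the issue is concealment rather than blinding. The article does not say whether this person is also the blinded neurophysiologist.
- **That the baseline questionnaire is completed in a session run by the injector, who already knows the arm.** The article gives the timing, not who is present or when the injector learns the allocation. Nor does it say that the injector sees patients at follow-up.
- **That fitting the input-output curves leaves the analyst free choice.** The Electrophysiological criteria section fixes the function, the fitting algorithm and the normalisation.
- **That the injector and the blinded ultrasound examiner are one person**, since both are called a rheumatologist and the injection is echo-guided. The Treatment section itself separates them, one as able to identify the drug and the other as blinded.

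**Conclusion.** The point holds in a limited form. The blinding rule in the Treatment section is broader than the reason given for it. It leaves questionnaire and VAS handling at follow-up, and the analysis, outside the blind without need. This rests on reading the sentence as the closed list that its wording makes it, and on these roles not being filled by one of the two blinded testers, which the article does not settle.

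The size is unknown. One could assume a differential shift of 0.1 to 0.2 points on the symptom score and set it against the planned difference of 2.0 - 1.6 = 0.4, giving 0.1/0.4 = 25% to 0.2/0.4 = 50%. Nothing in the document supports such a shift, so these percentages only restate the assumption and should carry no weight. With blinded raters for every outcome, severity is minor. This is a cheap improvement and does not show that the results would be biased.

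**What to change.** Replace the blinding sentence in the Treatment section with wording to this effect: Only the injecting rheumatologist and the holder of the randomisation list know the allocation. Baseline Boston Questionnaire and VAS are recorded before the allocation is disclosed to the injector. The injector does not administer or handle the questionnaire or the VAS at any visit. The patient, the ultrasound and electrophysiology testers, and those who handle the questionnaires, the VAS and the data are unaware of the arm. The data are analysed with arms coded A and B until the analysis, including the choice of post-hoc tests, is final.

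The cost is small. The change needs no added visit, measurement or staff: someone must already run the randomisation script and can hold the list, and one of the blinded testers, who see the patients at every visit, could hand out the forms. It does add one ordered step, disclosure to the injector after the baseline scores are in, and the code has to be held back until the analysis is final.

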### Sample size

The main output parameter is the Symptom Severity Scale (SSS) score of the self-administered Boston Carpal Tunnel Questionnaire. The values reported in the literature assessing the cortisone treatment effect after 2 and 3 months are ranging between 1.37 - 2.3 (mean ± standard deviation: 1.6 ± 0.7). It has been estimated that a minimum number of n = 26.2 subjects for each group would be necessary to reveal a significant (α = 0.05) decrease in the SSS score from 1.6 to 2.0 with enough power (90%). If a drop-out of 4 subjects is considered, the minimum number of subjects required should be adjusted to no. = 30.

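### The stated 26.2 per group matches a one-sample, one-sided formula; for the two-arm comparison the same inputs give about 52–59% power, not 90%

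*Protocol article*

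**What the plan says.** The Sample size section names the primary variable: "The main output parameter is the Symptom Severity Scale (SSS) score of the self-administered Boston Carpal Tunnel Questionnaire". It takes the post-cortisone score from the literature as "mean ± standard deviation: 1.6 ± 0.7" and sets the comparison at 1.6 versus 2.0 with 90% power. The result is a "minimum number of n = 26.2 subjects for each group would be necessary to reveal a significant (α = 0.05) decrease". It then adds: "If a drop-out of 4 subjects is considered, the minimum number of subjects required should be adjusted to no. = 30". No formula is named, the sidedness of the test is not given, and no visit is singled out. No correlation or other variance reduction is claimed.

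The design is described elsewhere. The Treatment section randomises patients to one of two groups, and Design of the trial gives a total of sixty women and asks whether progesterone does better than cortisone. Data analysis plans a "two-way ANOVA, with the main factors TREATMENT (cortisol vs progesterone) and TIME (baseline, 1 month, 6 months, and 12 months after the injection") at p < 0.05.

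**The concern.** The arithmetic and the design do not belong together. A size of about 26 for a standardised effect of 0.4/0.7 = 0.571 at 90% power is what one would expect for a single group, such as a before–after change or a mean tested against a fixed value. In a comparison of two independent means both arms contribute sampling error, so the number needed per arm is twice that of the one-sample formula. A two-sided test raises it further.

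At stake is how the result will be read. If the trial is reported as having 90% power, a non-significant difference looks like good evidence that progesterone is no better than cortisone. If the real power is little above one half, a true 0.4-point difference would be missed nearly half the time and a null result would say little.

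**Working it through.** **Inputs (all from Sample size unless noted)**

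- Difference: |1.6 − 2.0| = 0.4
- SD: 0.7, so the standardised difference is 0.571
- Alpha 0.05, power 90%: z = 1.645 (one-sided) or 1.960 (two-sided), and 1.2816
- Two independent arms (Treatment); 60 in total (Design of the trial), so 30 per arm
- Test: ANOVA F test at p < 0.05 (Data analysis), which has no direction

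**1. Reproducing the plan's figure**

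One sample, one-sided: n = [(1.645 + 1.2816) × 0.7/0.4]² = 8.564 × 3.0625 = 26.23. This agrees with the printed 26.2.

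**2. The other formulas at 90% power**

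| Comparison | n by normal formula | n by t test |
|---|---|---|
| One sample, one-sided | 26.2 | 27.6 |
| One sample, two-sided | 32.2 | 34.2 |
| Two samples, one-sided, per arm | 52.5 | 53.1 |
| Two samples, two-sided, per arm | 64.4 | 65.3 (so 66) |

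The two-sample formula is 2 × [(z₁ + z₂) × 0.7/0.4]². No two-sample version gives 26.2 per arm, and dropping to 80% power does not help (37.9 one-sided, 48.1 two-sided). The printed figure is 26.2/64.4 = 41% of the two-sided requirement.

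**3. Power of the trial as sized (two-sample comparison at one visit)**

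Normal approximation, two-sided:

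- n = 26: SE = 0.7 × √(2/26) = 0.194; 0.4/0.194 − 1.960 = 0.10; power 54%.
- n = 30: SE = 0.7 × √(2/30) = 0.181; 0.4/0.181 − 1.960 = 0.25; power 60%.

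Noncentral t:

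| Evaluable per arm | Two-sided | One-sided | Difference detectable with 90% power (two-sided) |
|---|---|---|---|
| 26 | 52.4% | 65.1% | 0.64 |
| 30 | 58.6% | 70.6% | 0.60 |
| 66 | 90.3% | – | 0.40 |

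**4. Power of the planned ANOVA**

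This needs assumptions that the article does not give. I take a constant 0.4 difference at 1, 6 and 12 months, no difference at baseline, and an equal correlation ρ of 0.3 to 0.7 between visits.

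- TREATMENT main effect: with baseline included the average difference is 3 × 0.4/4 = 0.3, with variance 0.49 × (1 + 3ρ)/4. Power falls from 59% to 41% as ρ rises (26 per arm), or from 66% to 46% (30 per arm).
- TREATMENT × TIME interaction: power rises from 39% to 78% (26 per arm), or from 45% to 84% (30 per arm).

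None of these reaches 90%.

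**5. What would make 26.2 per arm sufficient**

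The variance would have to shrink to 26.2/64.4 = 0.407 of its stated value. Adjustment for baseline multiplies it by 1 − ρ², so ρ would have to be √(1 − 0.407) = 0.77 for a two-sided test (0.71 one-sided). Alternatively the SD would have to be about 0.45 (0.49 one-sided) rather than 0.7. None of this is claimed.

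**6. Drop-out step**

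26.2 rounds up to 27, and 27 + 4 = 31. Thirty less four leaves 26, just under the stated minimum. This supposes that the four are lost from each arm.

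**The case against.** The core arithmetic is hard to contest, but several qualifications are fair.

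- **The formula is inferred.** The article names none, and 26.2 also results if the one-sided two-sample size of 52.45 per arm was taken as a total and halved. This is right, so *matches* is the proper word. The shortfall is the same by either route.
- **Sidedness is not stated.** The sample-size text speaks of a decrease and the objective of greater benefit, both directional. A one-sided reading gives 65% to 71%, better but still far from 90%, and the planned F test is not one-sided.
- **52–59% is the power of a single-visit t test, not of the planned ANOVA.** This is also right. The power of the ANOVA depends on unstated correlations and on which term is tested, and runs from about 39% to 84% under the assumptions above. The single-visit figure is a benchmark; the conclusion that 90% is not reached does not depend on it.
- **A better analysis could recover power.** Averaging the 6- and 12-month scores with adjustment for baseline gives, with 26 per arm, 77%, 81.5% and 92% at ρ = 0.3, 0.5 and 0.7. That is a reason to consider such an analysis. It does not justify the printed claim, which mentions neither the adjustment nor a correlation.
- **The drop-out slip is trivial.** Agreed: 27 instead of 26 per arm moves two-sided power only from 52.4% to 54.0%. If the four drop-outs are a total over both arms, 28 per arm remain and there is no shortfall against 26.2.
- **The aim is superiority, and nothing in the article proposes to read a null result as equivalence.** True. The risk lies in how readers will take a null result that carries a 90% power label.

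**Conclusion.** The point holds. The printed inputs and the printed size disagree for the design described. For 90% power, a two-arm comparison of a 0.4-point SSS difference with SD 0.7 at alpha 0.05 needs about 65–66 evaluable patients per arm two-sided, or 53–54 one-sided, against 26.2 stated and 30 enrolled. At a single visit the real power is 52% to 59% two-sided. So 41% to 48% of true 0.4-point differences would be missed, and only differences of 0.60 to 0.64 are detectable with 90% power.

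This rests on the article's own difference, SD and alpha, on equal arms, and on an unadjusted comparison. Only a variance reduction that the article does not claim would alter it materially. A fuller analysis plan could add detail but could not make the printed statement true. The drop-out rounding is a minor matter in the same paragraph.

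**What to change.** Keep 60 patients and rewrite the Sample size paragraph:

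1. Remove the statement that 26.2 per group gives 90% power.
2. State the test (two independent arms, two-sided alpha 0.05) and the visit to which the calculation applies.
3. Give the actual figures: with SD 0.7 and 26 to 30 evaluable per arm, power is 52% to 59% for a 0.4-point difference, and 90% for a difference of 0.60 to 0.64.
4. If a baseline-adjusted analysis averaged over the 6- and 12-month visits is adopted, give the power of that analysis with its assumed correlation: about 77% to 92% with 26 per arm for correlations of 0.3 to 0.7.
5. Say whether the four drop-outs are per arm or in total, and round up.
6. Correct the direction: a move from 1.6 to 2.0 is an increase on a scale where high scores mean worse symptoms. This does not affect the arithmetic.

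The cost is wording only. No patients are added and no procedure changes, but the stated power becomes less favourable. Retaining the 90% claim for an unadjusted single-visit comparison would instead require 2 × 66 = 132 evaluable patients.

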### Design of the trial

Sixty women with idiopathic mild CTS will be evaluated at before (baseline), 1, 6 and 12 months after injection.

The major outcome of this study is to determine that locally-injected progesterone may be more beneficial than cortisone in carpal tunnel syndrome at clinical level (SSS-BQ, VAS). Secondary outcome measures are:

- duration of experimental therapy, with a short (after 1 month) and long follow-up (after 6 to 12 months);

- improvement of electrodiagnostic and ultasonographic anomalies at various follow-up;

- correlation of the neurophysiologic and ultrasonographic data with clinical evaluation;

- comparison of the beneficial and harmful effects of the cortisone versus progesterone.

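### The sample-size paragraph plans for progesterone scoring 0.4 points worse than cortisone, the opposite of the trial's aim, and 30 per arm does not give the stated 90% power for a 0.4 difference

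*Protocol article*

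**What the plan says.** The Sample size section names the endpoint: "The main output parameter is the Symptom Severity Scale (SSS) score of the self-administered Boston Carpal Tunnel Questionnaire". It takes the cortisone value from the literature at 2 and 3 months ("mean ± standard deviation: 1.6 ± 0.7", range 1.37 to 2.3). It then sizes the trial at 26.2 per group, α = 0.05, for a "decrease in the SSS score from 1.6 to 2.0 with enough power (90"%). An allowance of 4 dropouts brings this to 30 per group, 60 in all.

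The Clinical criteria section fixes the scale. On the items, "they are scored 1 to 5 according to the severity of symptoms or the difficulty of performing a certain activity". For the total, "Each score is calculated as the mean of the score of individual item". For direction, "Severe impairment is indicated by a high score".

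The Design of the trial section gives the aim, that "locally-injected progesterone may be more beneficial than cortisone in carpal tunnel syndrome at clinical level (SSS-BQ, VAS"), and sets the visits at baseline and 1, 6 and 12 months. The article states no non-inferiority or equivalence margin.

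**The concern.** A decrease cannot run from 1.6 to 2.0. If the numbers are right and the word is wrong, the trial is planned around progesterone leaving patients with more symptoms than cortisone. If the word is right, at least one number is wrong or the numbers are not scores. This paragraph contains the trial's only planning alternative and the only justification for 60 patients. As written, a reader cannot tell what effect the trial is meant to detect, at which visit, or with what power.

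**Working it through.** **Inputs.** Cortisone mean 1.6, SD 0.7, second value 2.0, α = 0.05 (sidedness not stated), power 90%, 26.2 then 30 per group (Sample size). Item range 1 to 5, score as item mean, high = worse (Clinical criteria). Superiority aim and visits (Design of the trial).

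**1. Direction.** 2.0 − 1.6 = +0.4 on a scale where higher is worse. Suppose progesterone truly averaged 2.0 against 1.6 with SD 0.7. The standard error at 30 per arm is 0.7 × √(2/30) = 0.181. The chance of a significant two-sided result in favour of progesterone is Φ(−1.96 − 0.4/0.181) ≈ 0.000015, below 0.01%.

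**2. Can one correction repair it?**
- *Change decrease to increase.* The sentence becomes coherent, but the trial is then powered to show progesterone worse.
- *Keep 1.6 for cortisone and reverse the sign.* Progesterone is then 1.6 − 0.4 = 1.2, only 0.2 above the minimum of 1.0, or 0.2/0.7 = 0.29 SD. The largest possible advantage over 1.6 is 0.6. The article never states 1.2; it follows only if 1.6 is the cortisone mean.
- *Swap the numbers (cortisone 2.0, progesterone 1.6).* The direction is right and the floor is less close, but this contradicts 1.6 as the cortisone mean.
- *Read both as falls from baseline (cortisone 1.6, progesterone 2.0).* The direction is right, but the sentence speaks of the score itself. A mean fall of 2.0 also requires a mean baseline of at least 2.0 + 1.0 = 3.0. The article gives no baseline value, so this is neither stated nor excluded.

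**3. Reproducing 26.2.**
- One-sample, one-sided: n = (SD × (z₀.₉₅ + z₀.₉₀)/δ)² = (0.7 × (1.645 + 1.282)/0.4)² = **26.2**. This matches the stated figure.
- One-sample, two-sided: (0.7 × (1.960 + 1.282)/0.4)² = 32.2.
- Two-sample, one-sided: 2 × 26.23 = 52.5, so 53 per arm.
- Two-sample, two-sided: 2 × 32.18 = 64.4, so 65 per arm.

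Only δ² enters, so reversing the sign leaves every one of these unchanged.

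**4. Power of the two-arm comparison** for δ = 0.4, SD 0.7: Φ(δ/(SD × √(2/n)) − z).

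| n per arm | δ/SE | two-sided 5% | one-sided 5% |
|---|---|---|---|
| 30 | 0.4/0.181 = 2.21 | 60% | 72% |
| 26 (after dropout) | 0.4/0.194 = 2.06 | 54% | 66% |

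**5. Difference detectable with 90% power at 30 per arm.** Two-sided: (1.960 + 1.282) × 0.181 = 0.59 (0.60 with the t distribution). One-sided: (1.645 + 1.282) × 0.181 = 0.53.

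**The case against.** The strongest defence is that this is a slip of wording. The formula uses the absolute difference, so the sign has no effect on the number of patients, and a reader can guess that the two figures were transposed or are falls from baseline. Part of this stands. The sign alone does not change the sample size, and neither kinder reading is excluded. However, each conflicts with or adds to what the section says, so the article does not settle which was meant.

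A reader might go further and infer that superiority is unattainable because 1.2 lies against the floor. A normal curve with mean 1.2 and SD 0.7 would put 39% of scores below 1.0, and one with mean 1.6 already 20%. The documents do not support that conclusion. The value 1.2 is inferred. A mean of 1.2 with SD 0.7 is possible on a 1 to 5 scale (maximum SD √(0.2 × 3.8) = 0.87), though very skewed. A comparison of means at about 30 per arm does not require normal individual scores. If the progesterone SD shrank to between 0.2 and 0.5 (an assumption), the two-sided requirement would fall to about 35 to 49 per arm.

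A reader might also dismiss the change-score reading because patients are mild. The article defines mild by absence of objective deficits and by conduction class, with no limit on the symptom score.

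Finally, the planned analysis uses repeated visits, and adjustment for baseline could raise power. Reaching 26.2 per group in a two-arm comparison that way needs a baseline correlation of about 0.71 one-sided (1 − 26.2/52.5 ≈ 0.50, the square of 0.71) or 0.77 two-sided. No correlation is stated, and the ANOVA described in Data analysis names only treatment and time as factors.

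**Conclusion.** The planning alternative is wrong as written: it describes a 0.4-point worsening relative to cortisone, against a superiority aim and with no margin that would make 2.0 a tolerated limit. This follows from the article's own text and needs no outside source. Which correction was intended cannot be determined from the article.

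The numerical consequence comes from the formula, not the sign. For a difference of 0.4, power at 30 per arm is about 60% two-sided (72% one-sided), and at 26 per arm 54% (66%), instead of 90%. These figures assume a single-visit comparison of two arms, a common SD of 0.7, a normal approximation and no baseline adjustment; the t distribution lowers them by about 1 to 2 percentage points.

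**What to change.** Rewrite the Sample size paragraph so that it states:
- whether the figures are scores at a visit or changes from baseline;
- the expected mean in each arm, with progesterone the better one, and the source or assumption behind each;
- the visit they refer to, which must be 1, 6 or 12 months, because the present values come from 2 and 3 months, when no visit takes place;
- the SD for that quantity, and whether α = 0.05 is one- or two-sided;
- power from a two-sample formula at 30 per arm and at 26 after dropout. If baseline adjustment is relied on, the assumed correlation must be given.

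The quoted range of 1.37 to 2.3 describes cortisone at 2 and 3 months. It cannot serve as evidence for a progesterone mean or for a later visit, so values there should be labelled as assumptions and shown over a range.

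**Cost.** Rewording and a short recalculation. No extra patients or visits are needed if the power is simply restated, but the figure becomes less favourable. Keeping 90% power for 0.4 with SD 0.7 would instead take 53 per arm one-sided or 65 two-sided before dropout (106 or 130 in total).
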